## Abstract

Background: Fibromyalgia (FM) is defined as a chronic syndrome characterized by diffuse musculoskeletal pain, associated with characteristic signs and symptoms such as fatigue and/or sleep and mood disorders, and whose etiology, pathogenesis and prognosis may or may not be known. There is growing evidence of manual therapy as a treatment for pain in the short and medium term, also in patients affected by FM. However, the heterogeneity of the manual therapy treatments administered are a very common clinical practice, as they are based more on the judgment or tendency of the physiotherapist, rather than on clear scientific evidence. Therefore, the aim of the present study protocol will be to determine which manual therapy approach is more effective in addressing health status by improving symptoms (sensory, cognitive, emotional and social) in patients with FM. Methods: a randomized controlled clinical trial with a 3-month follow-up will be carried out with 52 female patients affected by rheumatologist-diagnosed FM will be recruited and evaluated at the Asociación de Fibromialgia y Síndrome de Fatiga Crónica (AFINSYFACRO) in Móstoles, Madrid, Spain. For more details on the protocol, a pilot study was carried out using a non-probability method of judgmental or purposive sampling. Thirteen patients were also evaluated, treated and reevaluated; eight patients were assigned to the myofascial techniques approach (MTA) group and five to the Maitland’s mobilization approach (MMA) group. Results: the preliminary results presented here are intended to show how the planned randomized controlled clinical trial will develop. Patients who received MTA had significantly improved pain and health status outcomes after treatment and at 1-month follow-up, with no significant change in those who received MMA. Conclusions: the exact details of the study protocol on which the manual therapy approach is more effective in addressing health status by improving symptoms (sensory, cognitive, emotional, and social) in patients with FM are presented. Preliminary results show that manual therapy is effective in improving pain and health status in patients with fibromyalgia at short and medium term, with significant results in those who received MTA.

## 1. Introduction

Fibromyalgia (FM), recognized as a clinical entity by the World Health Organization in the tenth revision of the International Classification of Diseases (1991) [1], is defined as a chronic syndrome characterized by diffuse musculoskeletal pain, associated with characteristic signs and symptoms such as fatigue and/or sleep and mood disorders. The etiology, pathogenesis and prognosis of FM are not fully understood [2,3,4].

The worldwide prevalence of this syndrome is 2.1%, being higher in women than in men with a ratio of 4:16. In the USA there are 26,400,000 people affected by FM [4]. Data close to the global figures are observed in Spain, where it affects 2.4% of the population over 20 years of age, mostly women [2]. 

It involves high direct costs (medical visits, complementary tests, pharmacological and non-pharmacological treatments) and indirect costs (reduction in working hours, sick leave and permanent disability). The cost per patient/year, in studies carried out in the USA and Spain, is between 7813 EUR and 9982 EUR, which implies an annual cost of more than 12,993 million euros [5]. 

This pathology does not have a firm and recognized organic etiology, so its pathogenesis is not yet fully defined. However, some authors postulate that various factors could be involved, among them: dysfunctions of the nervous, immune and endocrine system, environmental stressors and psychiatric or psychological issues [6].

Fibromyalgia is considered part of the group of central sensitization syndromes [7], and is defined as a hyperreactivity or amplified response to a stimulus by the nociceptive neurons in the CNS, and its etiology is multifactorial [8,9]. Although the pathophysiology of this process is still unclear, the windup phenomenon (increased neuronal excitability at the medullary level) and the alteration of descending inhibitory systems (modulators of the medullary response to nociceptive stimuli) [9] are considered.

Patients with FM presents a wide variety of symptoms and signs; among the most frequent are diffuse musculoskeletal pain, primary and secondary hyperalgesia, allodynia, stiffness, fatigue, asthenia, anxiety, depression, and sleep and mood disorders. In addition, it usually manifests together with concomitant pathology such as irritable bowel disease, headaches, neurological or rheumatic disorders or temporomandibular joint disorders [6,8,10,11].

The use of conventional analgesics is not usually effective in pharmacological treatment and so-called pain-modulating drugs, including antidepressants and antiepileptics, are prescribed; however, the proportion of patients who achieve an improvement in symptoms is very small [12]. 

There is high evidence of treatment combining exercise, aquatic exercise, other active therapies and multimodal therapies, on improving pain intensity, disability and physical function in the short term. In addition, manual therapy, needle therapies and patient education also provide short-term benefits [13].

In recent years, evidence is growing that manual therapy is a medium-term treatment for pain, also in patients affected by fibromyalgia [14,15,16,17]. However, the heterogeneity of the manual therapy treatments administered are a very common clinical practice, as they are based more on the judgment or tendency of the physiotherapist, rather than on clear scientific evidence.

Although the mechanisms of manual therapy have not been fully elucidated, its effect is explained by a mechanical stimulus that initiates a cascade of peripheral and central neurophysiological effects that are related to a decrease in the concentration of proinflammatory mediators, in addition to a decrease in mechanical hyperalgesia, and a stimulation of the supraspinal inhibitory pathways to produce a hypoalgesic response [14,15,16,17,18].

A recent published systematic review and meta-analysis [19] concluded that the myofascial techniques approach (MTA) improves pain, sleep, and quality of life compared to sham in patients with FM.

Accessory joint mobilizations (also known as Maitland´s Mobilizations) reduce pain, improve range of motion, and have effects that reflect an improvement in the autonomic profile through increased vagal activity, as well as an improvement in psychological factors associated with FM. [15,16].

Therefore, the aim of the present study is to determine which of the most commonly used manual therapy approaches in clinical practice is more effective in addressing health status by improving symptoms (sensory, cognitive, emotional and social) in patients with fibromyalgia.

## 2. Materials and Methods

### 2.1. Study Design

A randomized controlled clinical trial (RCCT) with a 3-month follow-up will be carried out between January 2023 and July 2023, with 52 female patients affected by rheumatologist-diagnosed FM who will be recruited and evaluated at the Asociación de Fibromialgia y Síndrome de Fatiga Crónica (AFINSYFACRO) in Móstoles, Madrid, Spain. The study protocol was approved by the Ethical Committee of the Rey Juan Carlos University, Madrid, Spain (reference number 2609202220822). In addition, the study was registered with ClinicalTrials.gov (NCT05559021), and will be conducted in accordance with CONSORT Statement 2010: updated guidelines for reporting parallel group randomized trials (CONSORT 2010 flowchart, Figure 1). According to the Declaration of Helsinki, all patients will sign an informed consent form before inclusion and must agree that their clinical information will be published anonymously. 

For more details on the protocol, a pilot study was carried out between January 2022 and July 2022 by recruiting thirteen patients using a non-probability method of judgmental or purposive sampling. The study protocol was approved by the Ethical Committee of the Rey Juan Carlos University, Madrid, Spain (reference number 2609202220822). All patients signed an informed consent form before inclusion.

### 2.2. Sample

Fifty-two consecutive patients younger than 65 years who meet the American College of Rheumatology (ACR) clinical criteria for FM [20] will be included in the study. Patients will be recruited by the center’s staff, who will be blinded to the severity of Fibromyalgia assessment performed. The center’s staff will be in charge of promoting the study through their direct contact, both in group activities and through individual talks. Individuals who will be included in the study will have a minimum one-year history of symptoms. To this medical diagnosis will be added a clinical evaluation based on the 2010 American College of Rheumatology (ACR) criteria [21], performed by the physical therapists and investigators participating in the study ([name] and [name]): given that 2 of the measurement variables that will be used in the study (widespread pain index, WPI; and symptom severity index, SS-Score) coincide with the protocol, when determining these criteria, the diagnosis of fibromyalgia will be corroborated when WPI ≥ 7 and SS ≥ 5 or WPI 3–6 and SS ≥ 9 [22]. The exclusion criteria will be: the receipt of any non-pharmacological therapy, presence of cardiac, renal or hepatic failure, severe physical disability, comorbidities (e.g., interstitial cystitis, inflammatory disease), infection, fever, hypotension, respiratory disorders limiting treatment, herpes, lupus, multiple sclerosis, rheumatoid arthritis, polio, epilepsy, rheumatic fever, cancer, history of neck or back surgery, skin disorders, psychiatric disease, non-compliance with the prescribed drug therapy, and pregnant women or with the possibility that they could be pregnant due to the incompatibility of the techniques [14,15,16,17,23].

In addition, out of twenty-three patients, thirteen finally met all the requirements and criteria and were recruited to present preliminary results by conducting a pilot study in order to provide a clearer description of the protocol.

#### Sample Size

The latest version of the free GRANMO program version 7.12 was used. The sample size of 52 randomly distributed patients will provide at least 80% statistical power to detect a difference of 14 units between the two groups in the FIQ inventory. This calculation assumes a bilateral significance level of 5% and a standard deviation of 17. In addition, a loss rate of 10% was calculated until the end of the study.

### 2.3. Intervention

There will be two intervention groups: myofascial techniques approach (MTA) group and Maitland’s mobilization approach (MMA) group. Both interventions were conceived and were (pilot study) and will be (RCCT) developed by clinicians and professors of Manual Therapy at the European University of Madrid (Spain), the Complutense University of Madrid (Spain), and CEU-San Pablo University of Madrid (Spain), with more than 15–20 years of clinical experience ([name]; [name]; [name]; [name]; [name]; and [name]). The research team includes two doctors in physiotherapy and four doctoral students, as well as a doctor in psychology. Only [name] had 2 years of clinical experience and a Master of Science degree.

#### 2.3.1. MMA Group

After a literature review of manual therapy treatments for fibromyalgia patients [16,24,25] and through a consensus of experts with 15–20 years of clinical experience, there was a decision to perform the following passive mobilizations approach for 1 session per week of 30 min each, for a total of 4 weeks.

The MMA group will be carried out with patient lying in a prone position, with the hands around the body and neck positioned comfortably. The therapist will perform postero-anterior joint mobilization using Maitland’s technique, applying pressure on the spinous process of the target vertebra (the one which most reproduces patient’s symptoms) [24]. Amplitude of mobilization will be done according to patient’s irritability, as other studies recommended [25]. Cycles of joint mobilizations will be applied to lumbar spine (Figure 2), thoracic spine (Figure 3) and cervical spine (Figure 4). 

In addition, it was decided to perform 3 sets of 2 min duration with 1 min of rest in each painful segment of the cervical, thoracic and lumbar spine. Spinal mobilizations have greater global, systemic and pain-modulating reflexogenic effects than peripheral joint mobilizations, so it was decided in expert consensus to select this approach targeting the spine with joint mobilizations [16,23,24,25].

#### 2.3.2. MTA Group

After a literature review of manual therapy treatments for fibromyalgia patients [14,17,19,26] and through a consensus of experts with 15–20 years of clinical experience, it was decided to perform myofascial techniques whose a systemic mechanism of action which best fit the picture of fibromyalgia disease. The MTA approach will consist of the application of the following myofascial techniques under the parameters of low load and long duration to the myofascial complex until the tissue restriction disappears with a frequency of 1 session per week of 30 min each, for a total of 4 weeks:-Transverse planes on the thoracolumbar fascia (TCL) and abdomen: the physical therapist, seated on one side of the table, places his hands facing each other so that one hand is between the table and the patient’s TCL and the other on the abdomen (leaving the navel between the first commissure) (Figure 5, myofascial technique 1).-Transverse planes at C7-D3 and sternum: the physical therapist, seated on one side of the table, places his hands facing each other so that one hand is between the table and the patient’s first 4 thoracic vertebrae (C7-T4) and the other on the sternum (thumb and index finger on each of the sternoclavicular joints) (Figure 6, Myofascial technique 2).-Suboccipital inhibition: in a first phase, the physiotherapist, seated at the head of the table, places his hands under the patient’s head transversely between the occipital and the spinous process of C2, so that the metacarpophalangeal joints are at 90° and the head is suspended with only this contact. In a second phase, the head is lowered in such a way that the occipital bone rests on the tenar eminences and a slight traction is maintained cranially (Figure 7, Myofascial technique 3).

**Figure 5 ijerph-20-01061-f005:**
[figure not shown]
Transverse planes on the thoracolumbar fascia (TCL) and abdomen (myofascial technique 1).

**Figure 6 ijerph-20-01061-f006:**
[figure not shown]
Transverse planes at C7-D3 and sternum (Myofascial technique 2).

**Figure 7 ijerph-20-01061-f007:**
[figure not shown]
Suboccipital inhibition (myofascial technique 3).

### 2.4. Randomization and Blinding

To ensure adequate blinding, participants will be randomly assigned to either the MMA (Maitland’s mobilization approach) group or the MTA (myofascial techniques approach) group immediately after they sign the informed consent forms. The randomization process will use numbers in sequential opaque envelopes. Patients will be asked not to comment on the treatment to other participants or to the evaluators. Details of adverse events will be recorded in a document which will be given to an administrator and completed separately by subjects in a room before the next session. Graph Pad software will be used to perform randomization, which will include the MMA group and the MTA group [27]. 

Thirteen patients were also evaluated, treated and reevaluated for the pilot study. Using a non-probability method of judgmental or purposive sampling, eight patients were assigned to the MTA group and five to the MMA group.

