### 2.5. Outcomes Measurement

The two primary outcomes will be assessed using the two assessment tools used in the 2010 American College of Rheumatology (ACR) FM diagnostic criteria, validated for use in the Spanish population, with a cut-off score of WPI ≥ 7 and SS ≥ 5 or WPI 3–6 and SS ≥ 9 [22]. [name] and [name] will be in charge of the post-treatment evaluation of the subjects, as well as the evaluation at each of the follow-ups, although all the questionnaires included are self-completed. Both members of the research team are clinicians with 10 years of daily experience, as well as professors of manual therapy at the European University of Madrid (Spain).

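### Section 2.4 claims adequate blinding, but the design only conceals allocation, and the unblinded patient rates every questionnaire outcome

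*Protocol article*

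**What the plan says.** All references are to the protocol article.

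- **Section 2.4** gives the purpose of randomisation as blinding: "To ensure adequate blinding, participants will be randomly assigned to either the MMA" group or the MTA group. Two concrete measures follow. One concerns how assignments are kept: "The randomization process will use numbers in sequential opaque envelopes". The other is a request made of the participants themselves: "Patients will be asked not to comment on the treatment to other participants or to the evaluators".
- **Section 2.3.1** describes the MMA treatment: "The MMA group will be carried out with patient lying in a prone position", with pressure on the spinous process of the target vertebra. **Section 2.3.2** describes MTA as sustained, low-load hand contact at the abdomen and thoracolumbar fascia, the upper thorax and sternum, and the base of the skull.
- **Section 2.5** puts two research-team members in charge of the post-treatment and follow-up evaluations, "although all the questionnaires included are self-completed". Of these two it says: "Both members of the research team are clinicians with 10 years of daily experience, as well as professors of manual therapy". Their university is the European University of Madrid.
- **Section 2.3** says of the treatments: "Both interventions were conceived and were (pilot study) and will be (RCCT) developed by clinicians and professors of Manual Therapy at the European University". This is the evaluators' university, and two others are given beside it. The section lists six people (names removed) and puts their experience at upwards of 15 to 20 years, apart from one with 2 years. It adds: "The research team includes two doctors in physiotherapy and four doctoral students, as well as a doctor in psychology".
- **Section 2.2** is the only place where anyone is expressly called blinded. These are the recruiting staff, and they are blinded to fibromyalgia severity, not to treatment.

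**The concern.** Random assignment makes the groups comparable at entry. Opaque envelopes stop anyone from foreseeing the next assignment. Neither keeps the patient, the therapist or the evaluator unaware of the treatment afterwards, so section 2.4 credits the design with a protection that it does not have.

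This matters here because the outcomes are subjective and reported by the patient. If she knows her treatment, any difference between arms in expectation, or in the wish to please, can enter her answers directly. A masked evaluator would not remove that. A report that repeated the claim of adequate blinding would lead readers to trust the WPI, SS, FIQ and NPRS comparisons more than the design allows.

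A second, smaller question is whether the two evaluators are independent of treatment. An evaluator who had treated the patient would know the allocation whatever the patient said or withheld.

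**Working it through.** **Step 1. Each stated measure and what it protects.**

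| Measure (section) | What it protects | Blinds the patient? | Blinds the evaluator? |
|---|---|---|---|
| Random assignment (2.4) | Comparability of groups at entry | No | No |
| Opaque envelopes (2.4) | Concealment of the next allocation | No | No |
| Request not to talk about treatment (2.4) | Evaluator masking, if patients comply | No; it presupposes that they know | Partly |
| Recruiters unaware of severity (2.2) | Recruitment | No | No |

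No row blinds the patient.

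**Step 2. Who rates the outcomes.** By section 2.5 the questionnaires are self-completed. Sections 2.3.1 and 2.3.2 describe treatments that differ in body position, site and type of contact. The rater is therefore someone who can tell which of the two she received, and this covers both primary outcomes.

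**Step 3. Are the evaluators separate from the treating team?**

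- *Pointing to overlap:* section 2.3 counts 2 doctors in physiotherapy + 4 doctoral students = 6, the same number as the people listed for the interventions; the seventh member is a psychologist. The evaluators are team members and manual-therapy professors at one of the same universities.
- *Pointing away from overlap:* the evaluators have 10 years of experience. The six have upwards of 15 to 20 years, except one with 2. Ten years fits neither description.
- *Not stated:* the verb in section 2.3 for what the six do in the trial is to develop the interventions. No sentence says who treats trial patients. The team list is introduced by a verb that need not be exhaustive.

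The text does not settle the question. If the evaluators are among the six, the experience figures contradict each other. If they are not, the team description is incomplete.

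**Step 4. Illustration of size.** Inputs from the Sample Size section: 52 patients, FIQ difference 14, SD 17, two-sided 5%, power 80%, loss 10%. A 1:1 allocation is assumed.

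The plan's own figure reproduces:
- n per arm = 2 × (1.960 + 0.842)² × 17² / 14² = 23.15
- 23.15 / 0.9 = 25.7, rounded up to 26 per arm, so 52 in total. (Rounding to 24 before adding losses gives 27 per arm, or 54.)

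With about 23 evaluable per arm (26 × 0.9 = 23.4), SE = 17 × √(2/23) = 5.01 FIQ units. With no true effect and a net reporting bias b between arms, the two-sided rejection probability is Φ(−1.96 + b/SE) + Φ(−1.96 − b/SE):

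| Assumed b (FIQ units) | b/SE | Rejection rate |
|---|---|---|
| 0 | 0 | 5.0% |
| 3 | 0.60 | 9.2% |
| 5 | 1.00 | 16.9% |
| 7 | 1.40 | 28.7% |

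A t-test version with 23 to 26 per arm agrees in pattern: b = 2, 4, 6 or 8 gives about 7%, 12–13%, 22–24% or 35–38%. Every value of b is assumed. FIQ is used because it is the only outcome with a planning SD. The sum is one two-group comparison, not the planned 2 × 5 repeated-measures ANOVA, and FIQ is not one of the two outcomes that section 2.5 calls primary.

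**The case against.** Patients cannot be blinded when two hands-on techniques are compared, and nothing proposed here would change that. Both arms are active, each with one 30-minute session a week for 4 weeks, so differential expectation should be smaller than against a sham or no treatment. The request not to talk to evaluators makes sense only if the evaluators are meant to be unaware of allocation, so some masking is intended. Self-completion limits what an evaluator can influence. Finer detail on roles may sit in a fuller protocol.

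All of this stands, and it limits the point to what section 2.4 claims and how the outcomes are then read. It does not rescue the claim: a design that cannot blind patients should not be described as adequately blinded.

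Three stronger readings are tempting, and the documents do not support them.

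- *A reader might infer that the evaluators treat the patients they assess.* The names are removed from the text at hand, which is not a fault of the plan. The head count rests on a list that may be incomplete, the experience figures point the other way, and no sentence says who treats.
- *A reader might infer, because the pilot favoured MTA, that bias will favour MTA.* Nothing says what trial patients are told about the pilot or the hypothesis, so the direction is unknown.
- *A reader might think that a baseline expectancy rating, used as a covariate, would repair the problem.* Randomisation balances such a rating on average, and adjusting for it does not remove a reporting bias that arises after patients learn their arm.

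**Conclusion.** The concern holds for the blinding claim. As written, section 2.4 presents random assignment as a means of blinding. What the design provides is allocation concealment and, at most, partial masking of evaluators. The patient who rates both primary outcomes, and FIQ and NPRS, is not blinded. This conclusion needs no assumption beyond the physical difference between the two treatments as described.

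The independence of the evaluators is an open question, not an established fault; sections 2.3 and 2.5 need reconciling on it.

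The size of any bias is unknown. The 9%, 17% and 29% figures show only how sensitive a comparison with an SE of about 5 FIQ units would be to biases of 3, 5 and 7 units. They are not estimates of this trial's error rate and should carry no weight in judging how serious the point is. The sample size and the planned analysis are unaffected.

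**What to change.** 1. **Section 2.4.** Replace the blinding claim with: allocation is concealed by opaque envelopes; participants and therapists are not blinded. Interpret the self-reported outcomes on that footing in the trial report.
2. **Section 2.5.** State that the two evaluators treat no trial patient and hold no allocation information. Reconcile the experience figures and team description in section 2.3 with those in section 2.5, so that the reader can see whether the two groups overlap.
3. **Section 2.5.** State that patients complete the questionnaires alone and hand them to the administrator who already receives the adverse-event forms under section 2.4.

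The cost is a few sentences and a split of roles within the team. The trial can no longer be called adequately blinded, and the two evaluators are not available to treat.

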### 2.6. Statistical Analysis

The distribution of quantitative variables will be analyzed with the Kolmogorov– Smirnov test, to evaluate the normality of the samples to verify if there are significant differences in the two samples at baseline, as well as at different times (*p* > 0.05). The t-test will be used for comparison of characteristics between the different groups at baseline. The chi-square test will be used to assess the independence of the categorical baseline data. The mean, SD and 95% CI will be calculated for all variables. Repeated-measures analyses of variance (ANOVA) with two factors (2 (treatment groups) × 5 (time: baseline, immediately after intervention, and at one month, two months and three months after the study started)) will be performed for the FIQ and NPRS scores. The comparisons for time factor for all variables and for each group will be applied to the group. Time comparisons for all variables and for each group the proportion of subjects who have an improvement than the NPRS MCID (2.0 points) or the FIQ MCID (14%) will be calculated and will be compared between groups using the *p* value [26,49]. The effect size will be calculated for the NPRS and FIQ variables. *p* values associated with F statistics will be adjusted for ANOVA via the Greenhouse–Geisser correction. Statistical significance will be set at *p* value of <0.05 for all calculations. 

For the analysis of the pilot study, the data were analyzed with the SPSS package version 25.0 (SPSS Inc, Chicago, IL, USA). The homogeneity of the sample in both groups was examined at the beginning of the study with respect to the variables studied to detect statistically significant differences using the Mann–Whitney U test. Descriptive statistics, including frequency counts for categorical variables and measures of central tendency and dispersion for continuous variables, were calculated to summarize the data. Paired-samples T-test was used to compare pre, post, and 1–2-month measurements of all variables studied. The Wilcoxon rank test for related samples was used to establish differences between scores before and immediately after the 4 treatment sessions, 1 month after the intervention and 2 months after the intervention in the two groups. For all study data, *p* values less than 0.05 were considered significant.

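### The one stated time for recording adverse events exists only after sessions 1 to 3, so the written procedure does not reach session 4, the follow-up or patients who stop

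*Protocol article*

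**What the plan says.** The only text on collecting adverse events is in section 2.4 (Randomization and Blinding) of the protocol article: "Details of adverse events will be recorded in a document which will be given to an administrator", and the form is "completed separately by subjects in a room before the next session". The same section asks patients not to discuss their treatment with the evaluators.

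The treatment schedule is the same in both arms. Section 2.3.1 gives the MMA group "1 session per week of 30 min each, for a total of 4 weeks", and section 2.3.2 describes the MTA group's techniques "with a frequency of 1 session per week of 30 min each, for a total of 4 weeks".

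Patients remain in the study well beyond treatment. Section 2.1 describes "A randomized controlled clinical trial (RCCT) with a 3-month follow-up". Section 2.6 lists the measurement times as "baseline, immediately after intervention, and at one month, two months and three months after the study started". Section 2.5 says that two members of the team "will be in charge of the post-treatment evaluation of the subjects, as well as the evaluation at each of the follow-ups". None of these sections attaches an adverse-event form to the later assessments.

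**The concern.** The article does more than stay silent on safety. It says who completes the form, where, who receives it and when, and the timing depends on an event that does not occur after the last session. Staff who followed the text literally would hand out no form once the fourth session was over.

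Three kinds of event would then have no described route onto the form: a reaction to the fourth session, an event that appears during follow-up, and an event after which the patient does not come back. The trial compares two hands-on treatments to see which is preferable, so a reader will want to know how well each is tolerated. The request not to discuss treatment with evaluators adds a little to the problem. The evaluators are the people seen at follow-up, and a patient might take the request as a reason not to mention a reaction to treatment. A structured form that bypasses the evaluators is therefore more useful at those visits.

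**Working it through.** The plan gives no figure of its own for adverse-event coverage, so the check is a count of sessions and weeks.

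**1. Occasions on which the form can be completed.** Sessions per patient: 1 per week × 4 weeks = 4 (sections 2.3.1 and 2.3.2).

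| After session | Is there a next session? | Form under section 2.4 |
|---|---|---|
| 1 | yes, session 2 | yes |
| 2 | yes, session 3 | yes |
| 3 | yes, session 4 | yes |
| 4 | no | none described |

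Coverage is 3/4 = 75% of treatment exposures. For 52 patients with full attendance this is 52 × 3 = 156 of 52 × 4 = 208 sessions. It is a ceiling, because a patient who stops after any session has no later form. The totals only restate 3 of 4; they do not estimate missed events.

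**2. Time without a described form.** Assume sessions at weeks 0, 1, 2 and 3, so that the last form falls at week 3. One month is 365.25/12/7 = 4.348 weeks, so three months is 13.04 weeks. The uncovered share is (end − 3)/end.

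| How the three-month visit is counted | End (weeks) | Uncovered (weeks) | Share |
|---|---|---|---|
| from study start, as section 2.6 words it | 13.04 | 10.04 | 77% |
| from the last session (week 3) | 16.04 | 13.04 | 81% |
| from the end of week 4 | 17.04 | 14.04 | 82% |

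These are shares of time and not of events. The article gives no event rate, so the number of unrecorded events cannot be estimated.

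**3. Whether another section fills the gap.** The instruments in sections 2.5.1 to 2.5.8 do not include an adverse-event form. The pain scales and the global rating of change would register worsening that is present at a visit, but they do not record an event, its date or its relation to treatment. Section 2.6 attaches no adverse-event item to any time point.

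**4. Whether the design figures are touched.** The Sample Size section says "The sample size of 52 randomly distributed patients will provide at least 80% statistical power" for a difference of 14 FIQ units, SD 17, two-sided 5% and 10% loss. The normal approximation gives 2 × (17 × (1.960 + 0.842)/14)² = 23.15 per arm. Then 23.15/0.90 = 25.72, rounded up to 26 per arm and 52 in total. The stated figure reproduces, and nothing in it depends on adverse-event recording.

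**The case against.** The strongest reply is that the sentence stands in a section on blinding. It explains how the form is kept away from evaluators and was not written as a safety schedule. It does not say that recording is confined to this moment or ends after session 4. The article condenses a fuller protocol, where follow-up of adverse events and of withdrawn patients would normally be set out. This stands in part. A reader might infer that events after the fourth session are never captured, but the article does not establish that. It shows only that the procedure it describes does not capture them. The reply does not remove the point, because the article chose to fix a time and the time it fixed cannot apply after the last session.

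Patients are also still seen after treatment, and the pain measures and global change scale would pick up some worsening. That is correct, and it is why one should not say that every delayed flare is missed.

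Two further inferences are tempting and unsupported:

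- **A biased harms comparison.** Section 2.6 plans no such comparison and section 2.5 does not list adverse events as an outcome. The number and spacing of sessions are the same in both arms, and one form is described for all patients. Nothing in the article shows a mechanism that would favour one arm.
- **A count of early stoppers affected.** The 10% loss is stated for the whole study and not split by phase. In the pilot all 13 patients completed treatment, and the one loss was at the two-month follow-up.

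**Conclusion.** The point holds as a badly fixed timing rule. The one recording time stated in the article exists after three of the four sessions. Followed literally, it leaves the fourth session, the follow-up and the period after a stopper's last attended session without a form. The uncovered share of time is about 77% to 82%, assuming weekly sessions from week 0 and full attendance, with the range reflecting how the three-month visit is counted.

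The conclusion rests on the article alone. If the full protocol already records events at the later assessments, what remains is to align the article's wording with it. There is no effect on sample size, power or the efficacy analysis, and no basis here for claiming that events will certainly go unrecorded or that one arm will look safer than it is. Severity is minor.

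**What to change.** Extend the timing in section 2.4. The same self-completed form should be filled in before sessions 2, 3 and 4, at the post-treatment assessment, and at the one-, two- and three-month assessments. Anyone who misses or stops sessions should complete it at the next contact. Each form should cover the period since the previous one, so that no interval is left out. Keep the present route, with the form completed apart from the evaluators and returned to the administrator, so that evaluators stay unaware of anything that might reveal the treatment.

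If the full protocol already provides for this, a sentence in section 2.4 saying so is enough.

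The assessments already exist, so no visit is added. The cost is one short form and a few extra minutes per visit, plus a contact for the patients who do not return.
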